#### Interim analyses {21b}

We anticipate there will be 2 formal interim efficacy analyses, after 1/3 and 2/3 of the information has accrued; however, the DSMB may alter the timing and number of efficacy analyses as required. The DSMB may recommend early termination of the trial based on these analyses. Such a recommendation would be made if, in the view of the DSMB, there is proof beyond reasonable doubt that the intervention is better than placebo control, or if there were significant safety concerns. The Haybittle-Peto boundary, requiring *p* < 0.001 at an interim analysis to consider stopping for efficacy, will be used as guidance.

Given the lack of data on event rates at the study sites at the time of protocol development, the DSMB will review the event rates before recruitment is completed, to consider the extension of recruitment if event rates are lower than anticipated.

#### Methods for additional analyses (e.g. subgroup analyses) {20b}

Analyses of secondary outcomes of (i) possible, probable or definite TB; (ii) TB incidence of death (all causes); and (iii) overall mortality will follow the same approach as for the primary outcome. For safety and completion of treatment outcome, we will compare the proportions of participants experiencing each event by arm using either *χ*^2^ or Fisher’s exact tests (depending on numbers of events). No formal adjustments are made for multiplicity across the secondary analyses, but results will be interpreted with appropriate caution.

Subgroup analyses will be conducted for the primary outcome, if the overall treatment effect is significant, by including interaction terms in the analyses. The pre-specified subgroup comparisons are area (Mbeya, Moshi, Uganda), age group (approximately tertiles), duration of DM (approximately tertiles), DM status (new vs known), BMI (as a continuous and categorical variable) and level of glycaemic control (HbA1c > 8%) at baseline. In addition, we will repeat the primary analysis (i) restricted to the group who are TST positive and (ii) restricted to the group who are IGRA positive.

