### Sample size {14}

We expect to screen approximately 6000 individuals in order to recruit 3000 patients with DM and LTBI for the RCT. In an unpublished case-control study (excluding HIV patients) in Uganda, the prevalence of LTBI among the DM patients as well as controls was ~ 70% using Quantiferon only.

With an incidence rate of 22.5 TB cases/1000/year, we will have 90% power to detect a RR of 0.5 or less with 3000 individuals randomised (allowing for 10% loss to follow-up). Sensitivity analyses to assess the power of our study under a range of plausible parameter estimates are shown in Table 4. Incidence rates of TB were estimated from prevalence studies, assuming an average disease duration of 2 years. With respect to efficacy, no data are available in DM patients, but a Cochrane Review of 12 trials with 8578 HIV-infected participants reported TB preventive treatment (any anti-TB drug) had a lower incidence of active TB than placebo (RR 0.68, 95% CI 0.54–0.85) [32]. The benefit was greater in TST-positive individuals (RR 0.38, 95% CI 0.25–0.57) than TST-negative individuals (RR 0.89, 95% CI 0.64–1.24) [28]. Risk reduction is expected to be at least as great for DM, and to justify policy change, we envisage that at least 50% efficacy would be needed. TB incidence is expected to stay relatively constant in people with DM (as opposed to the decreasing incidence observed in TB case contacts) which means it is worthwhile to continue follow-up for all trial participants until the last randomised participant completes 24 months of follow-up, in order to maximise power.

**Table 4 Tab4:** The total number of people needed (with 1:1 randomisation) for detecting a given reduction in risk with 90% power and a significance level of 0.025 (one-sided)

	Cumulative number of cases/1000 over 2 years of follow-up		
RR	30/1000	40/1000	50/1000
0.4	2664	1982	1574
0.5	4106	3054	2424
0.6	6834	5082	4032

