### Assignment of interventions: allocation

#### Sequence generation {16a}

Participants will be randomised 1:1 to intervention or placebo using blocked randomisation within strata (clinical sites), with random block sizes. The randomisation list will be generated and managed by a validated module in the CASTOR database.

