### Statistical methods

A summary of the statistical approaches is provided here. Full details are outlined in the Statistical Analysis Plan. All efficacy comparisons test hypotheses of the superiority of RPT/INH against placebo, with a significance level of 0.025 (one-sided).

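### Age, diabetes duration and HbA1c get only categorical interaction tests while BMI also gets a continuous one; if effect modification is roughly log-linear, this costs about 10 to 23 points of power

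*Protocol article*

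**What the plan says.** The protocol article, under Methods for additional analyses {20b}, says subgroup analyses of the primary outcome will be done "if the overall treatment effect is significant, by including interaction terms in the analyses". Among the pre-specified comparisons, four modifiers are measured on a continuous scale, and they are handled in three ways:

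- Age and diabetes duration: "age group (approximately tertiles), duration of DM (approximately tertiles"), without numerical limits.
- HbA1c: "level of glycaemic control (HbA1c > 8%) at baseline", one cut fixed in advance.
- BMI: "BMI (as a continuous and categorical variable").

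Only BMI has a continuous version. The Objectives section lists the subgroup comparisons as a secondary objective and words it as exploratory. The assessment schedule (Table 3) shows that HbA1c is measured before randomisation and that demographics and diabetes history are recorded at screening, so the continuous values will be available. The trial is sized for the overall effect: "With an incidence rate of 22.5 TB cases/1000/year, we will have 90% power to detect a RR of 0.5 or less". That statement rests on a total of 3000 participants and includes a 10% allowance for loss. No power is stated for any interaction test.

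**The concern.** Grouping a continuous modifier discards the variation within each group. If the effect of 3HP changes gradually with age, diabetes duration or HbA1c, a grouped interaction test detects the change less often than a test on the measured value. The trial expects only about 90 to 125 TB events (derived in the working), so interaction tests have little power to begin with. The article already accepts the continuous approach for BMI, which makes its absence for the other three hard to explain. At stake is the trial's ability to say whether efficacy varies with these characteristics, which is a secondary, exploratory question.

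**Working it through.** **Inputs from the article.** Control incidence 22.5/1000/year, RR 0.5, 3000 randomised, 10% loss, 90% power (Sample size {14}); one-sided 0.025 for efficacy comparisons (Statistical methods); 1:1 allocation (Sequence generation {16a}); Poisson regression (Statistical methods {20a}); at least 24 months of follow-up and 18 months of accrual.

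**Assumptions, not in the article.** A normally distributed modifier, a log rate ratio linear in it, and a two-sided 5% interaction test. The share of participants with HbA1c above 8% is not given, so several splits are shown.

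**1. The plan's own figure.** Two-year risks are 0.045 and 0.0225, with mean 0.03375. With pooled variance under the null,

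n per arm = [1.960·√(2·0.03375·0.96625) + 1.282·√(0.045·0.955 + 0.0225·0.9775)]² / 0.0225² ≈ 1352.

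The total is 2704, and 2704/0.9 gives 3005 against the stated 3000. Power with 2700 evaluable is 90.0%. All nine totals in Table 4 reproduce exactly.

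**2. Expected events.** With 1350 evaluable per arm over two years: 1350·0.045 ≈ 61 control and 1350·0.0225 ≈ 30 treated, about 91 in all. If mean follow-up is 24 + 18/2 = 33 months (assuming even accrual), 91·33/24 ≈ 125.

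**3. Sensitivity of a continuous test.** With one third of D events in the treated arm, the information on the interaction per SD is about D·(1/3)·(2/3). For 80% power the log interaction must be (1.960 + 0.842)/√(2D/9).

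- D = 91: 2.802/4.50 = 0.623, a 1.86-fold change in rate ratio per SD.
- D = 125: 2.802/5.27 = 0.532, a 1.70-fold change.

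The first means a rate ratio of 0.5/1.86 = 0.27 at one SD below the mean and 0.5·1.86 = 0.93 at one SD above. Only strong modification is detectable, even with the best coding.

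**4. Information kept after grouping.** This is Σ pₖmₖ², where pₖ is the share in group k and mₖ its mean in SD units.

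- Tertiles (cuts at ±0.431 SD; outer means ±1.091, middle 0): (2/3)·1.091² = 0.79.
- Median split: 2/π = 0.64.
- 30/70 split: φ(0.524)²/(0.3·0.7) = 0.1209/0.21 = 0.58.
- 20/80 split: 0.0784/0.16 = 0.49.

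**5. Power.** The continuous test with 80% power has noncentrality 2.802² = 7.85. Multiplying by the information kept and referring to a noncentral chi-square gives:

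| Coding | Information | Power when continuous has 80% | Power when continuous has 50% |
|---|---|---|---|
| Tertiles as trend, 1 df | 79% | 70% | 42% |
| Tertiles unordered, 2 df | 79% | 60% | 33% |
| Median split | 64% | 61% | 35% |
| 30/70 split | 58% | 57% | 32% |

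**6. Simulation check.** Poisson models, 1000 replicates, 2700 participants, two years, RR 0.5 at the modifier mean. Type I error was 4 to 5% for every coding.

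| Change in rate ratio per SD (mean events) | Continuous | Tertile trend | Tertiles 2 df | Median split | Cut isolating top 30% |
|---|---|---|---|---|---|
| 1.35 (91) | 28% | 22% | 17% | 19% | 18% |
| 1.65 (93) | 62% | 53% | 43% | 45% | 45% |
| 1.88 (95) | 84% | 73% | 64% | 62% | 66% |

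**7. Modest modification.** A further simulation at control risk 0.045 gave, for 1.2 per SD, 13% continuous, 10.5% median split and 10% tertiles; for 1.3 per SD, 23%, 16.5% and 13%.

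**The case against.** The strongest reply is that the article calls itself a summary and sends full details to the statistical analysis plan, where coding and cut points normally sit. This stands for the tertile limits: their absence from the article is no fault. It does not dispose of the point, because the article does state the form of each modifier and names a continuous form for BMI alone.

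Second, categories have real uses. They do not assume linearity, they give efficacy by group in a form clinicians can read, and if modification is a threshold near the cut, grouping need not lose power. Diabetes duration, with newly diagnosed participants included, may be neither normal nor linear in its effect. This stands, and it is why the categories should stay.

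Third, the analyses are exploratory, run only after a significant overall effect, and secondary results are to be read with caution. This stands and limits the importance of the point.

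A reader might infer that the cut points are data-driven. For HbA1c this is wrong, since 8% is fixed in advance. For the tertiles it is only an inference: an approximate-tertile rule on baseline values need not depend on outcomes, and nothing in the article says that it will.

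A reader might also suppose that an off-centre HbA1c cut always loses more than a median split. That is true of the information measure in step 4 but not in general. With the strongest modification in step 6, isolating the top 30% gave 66% against 62% for the median split. In another simulation (control risk 0.055, 1.5 per SD), isolating the top 30% gave 39%, the median split 37% and isolating the bottom 30% gave 33%. The direction of the cut matters.

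**Conclusion.** The point holds as a minor weakness. Under roughly log-linear modification of a roughly normal covariate, tertiles lose about 21% of the information and one cut about 36% or more. Where a continuous test would have 80% power, the loss is about 10 points for a tertile trend, 20 for unordered tertiles and 19 to 23 for a single cut between 50/50 and 30/70. The article does not say whether the tertiles would be tested as a trend or as unordered groups.

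These figures depend on the assumed shape. A threshold near the cut would shrink or remove the loss. With modest modification, power is low whatever the coding, so the change improves these tests without making them strong.

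Two larger conclusions are not supported. One is that the choice compromises a central question of the trial: the primary objective is overall efficacy, glycaemic control is one of several exploratory subgroup factors, and the primary result is unaffected. The other is that grouping brings no benefit, since it has the descriptive uses given above.

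**What to change.** Extend the approach already stated for BMI to age, diabetes duration and baseline HbA1c. Test each interaction on the continuous value and check linearity, for example with a spline. Keep the tertiles and the 8% cut for presenting efficacy by group, with the tertile limits fixed before unblinding.

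The cost is a change of wording in the analysis plan and three extra model terms, with no new data, visits or participants. The small downside is reliance on a linearity assumption, and with so few events the check can reveal only gross departures.

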#### Methods in analysis to handle protocol non-adherence and any statistical methods to handle missing data {20c}

Per-protocol analysis will be used as a secondary analysis of the primary endpoint. In the per-protocol analysis, only patients who receive the study drug as planned will be analysed; this will exclude patients who did not complete treatment and participants with major protocol violations.

The primary analysis will not adjust for missing data, but multiple imputation will be carried out as a sensitivity analysis to account for data that are missing at random (MAR). In addition, sensitivity analyses will be carried out to evaluate the robustness of the conclusions to a range of plausible patterns of missing not at random (MNAR) using pattern mixture or selection models.

### Plans to give access to the full protocol, participant-level data and statistical code {31c}

The protocol will be readily available; however, corresponding data generated from this trial will not be for the public. The PROTID trial has been registered in the clinicaltrials.gov identified with NCT04600167 since 23 Oct 2020.

## Oversight and monitoring

### Composition of the coordinating centre and trial steering committee {5d}

Overall project management and progress monitoring will be performed by the Executive Group (EG). The EG will be led by the project coordinator and the trial responsibility will be with the trial sponsor. Preferably, decisions will be made by consensus; otherwise, the matter will be discussed with the DMC and Scientific Advisory Board (SAB) in order to make a decision if necessary. The day-to-day work of the project will be handled by the field sites that also coordinate local regulatory, diagnostic work and data management. Sites will report progress and receive guidance from the trial sponsor and EG. EG members will meet regularly with a frequency of at least a month, which can be intensified based on the current need. A SAB has been formed to provide independent advice to the trial. The SAB will meet at least annually and discuss overall scientific strategy and progress. In addition, an independent DSMB has been established with its primary responsibility being to safeguard the interests of trial participants by monitoring participant safety, assess participant risk versus benefit and assess data quality. The management approach is described graphically on the project organogram (Fig. 2).

**Fig. 2 Fig2:**
[figure not shown]
Project organogram with Work Package (WP) 2 representing the PROTID trial

### Composition of the data monitoring committee, its role and reporting structure {21a}

The DSMB is composed of five members, with clinical and methodological expertise, including an independent statistician. The DSMB will review results at regular intervals, blinded to treatment allocation in the first instance, but may be unblinded if deemed necessary in consultation with the project EG. Access to interim data and results on study safety or efficacy will be confidential and strictly limited to the DSMB.

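### The only described route for unblinding the DSMB runs through the Executive Group, so a request prompted by an interim signal would itself inform trial management

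*Protocol article*

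**What the plan says.** Three sections of the protocol article bear on this.

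- **Composition of the data monitoring committee {21a}.** The DSMB reviews results periodically, "blinded to treatment allocation in the first instance, but may be unblinded if deemed necessary in consultation with the project EG". The next sentence reads: "Access to interim data and results on study safety or efficacy will be confidential and strictly limited to the DSMB". The board has five members, one of them an independent statistician.
- **Composition of the coordinating centre and trial steering committee {5d}.** The EG carries out overall project management and progress monitoring.
- **Interim analyses {21b}.** The plan anticipates "2 formal interim efficacy analyses, after 1/3 and 2/3 of the information has accrued", and the DSMB may change their number and timing. It may recommend stopping if "there is proof beyond reasonable doubt that the intervention is better than placebo control", with p < 0.001 as guidance, or for significant safety concerns. Separately, "the DSMB will review the event rates before recruitment is completed, to consider the extension of recruitment" if rates are lower than anticipated.

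**The concern.** The stopping criterion has a direction. A board looking at coded arms can see that they differ, but not whether the active arm is the better or the worse one, and those two answers call for opposite recommendations. A board that starts blinded therefore needs the code at the moment a difference appears. The only way to the code that the article describes is consultation with the group running the trial.

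The consultation then carries information. The EG need not see a single number: an unscheduled request for allocation soon after an interim analysis tells it that something in the data prompted the board. That sits against the sentence confining interim information to the DSMB. What is at stake is the conduct of the trial by people who should have no hint of the interim comparison, and the board's independence when it needs to know which arm is affected. The Discussion already concedes that discolouration of body fluids may compromise blinding, so a further source of information is unwelcome.

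**Working it through.** **Text against task**

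1. Stated task: judge superiority over placebo and act on safety concerns ({21b}). Both need arm identity.
2. Stated starting position: blinded ({21a}).
3. Stated route from 2 to 1: if deemed necessary, in consultation with the EG ({21a}). No other route appears.
4. Stated protection: interim data and results go to the DSMB alone ({21a}). This covers data and results. It does not cover the fact that a request was made.

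Steps 3 and 4 conflict in effect whenever the request is prompted by the data.

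**How likely and how informative is a signal?**

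Inputs from Sample size {14}: control incidence 22.5/1000/year (0.045 over 2 years), rate ratio 0.5 (0.0225), 3000 randomised, 10% loss. Evaluable per arm: 0.9 × 1500 = 1350. Alpha is one-sided 0.025.

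*Reproducing the plan's power.* With the pooled variance under the null, p̄ = 0.03375:

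z = [0.0225 × √1350 − 1.960 × √(2 × 0.03375 × 0.96625)] / √(0.045 × 0.955 + 0.0225 × 0.9775) = (0.8267 − 0.5005) / 0.2549 = 1.280

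Power = 89.97%, against the stated 90%. All nine totals in Table 4 also reproduce with this formula.

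*Events, counting 24 months of follow-up.* 1350 × 0.045 × 1.5 = 91.1 in total, so 30.4 at one third and 60.75 at two thirds.

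*Chance of crossing under rate ratio 0.5.* With Var(log RR) ≈ 4/d, the expected z is (√d / 2) × ln 2. The article does not give the sidedness of p < 0.001, so both critical values are shown.

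| Look | d | Expected z | One-sided, 3.090 | Two-sided, 3.291 |
|---|---|---|---|---|
| 1 | 30.4 | 1.910 | 11.9% | 8.4% |
| 2 | 60.75 | 2.701 | 34.9% | 27.8% |

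With no effect, the chance in the efficacy direction is 0.1% per look (one-sided reading) or 0.05% (two-sided reading). At the first look a crossing is thus about 0.119 / 0.001 = 119 times as likely under rate ratio 0.5 as under no effect.

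**Planning value for a pooled event-rate review**

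22.5 × (1 + 0.5) / 2 = 16.9/1000/year.

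**Does the first interim fall together with the extension decision?**

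Assume uniform accrual of 3000 over the 18 months given in Recruitment {15}.

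- *24-month basis:* 30.4 / 0.016875 = 1800 person-years. Person-years at month m are (3000/18) × m² / 24, which gives m = 16.1.
- *Follow-up to the end of the trial, as {14} states:* mean follow-up is 24 + 9 = 33 months. Without loss, total events are 3000 × 2.75 × 0.016875 = 139, and one third is 46. By month 18 there are 2250 person-years and 38 events. The rest accrue at 250 person-years a month, so the look falls at about month 20.
- *Low event rate, 24-month basis:* at 13.5/1000/year the look moves to 30.4 / 0.0135 = 2250 person-years, or month 18.0. At 12/1000/year it moves to about month 19.1.

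The two coincide only on the first basis and at the planned rate.

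**The case against.** The strongest reply is that the article describes no leak. Consultation is not approval, the EG is given no veto, and the confidentiality sentence bars the passing of data or results. This stands as far as it goes: the exposure is the request and its timing, nothing more.

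Second, consultation could be settled in advance for the scheduled interims, in which case it would carry no signal. That would help, but the article does not say it. Blinding at first, with unblinding where judged necessary, describes case-by-case decisions.

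Third, a masked board can compute whether p < 0.001 between coded arms. True, but the criterion is superiority over placebo, and direction needs the code.

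Fourth, the interims are only anticipated and the board may change them, and no sentence says that EG consultation is the sole route. Both are fair. The point is that it is the only route described.

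Fifth, closed-report arrangements belong in a DSMB charter, which a journal article need not reproduce. That would answer a complaint about missing detail. Here the article states a rule, and if a charter says otherwise the two must be reconciled.

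On recruitment, the review is naturally read as a check of overall event rates, since it is motivated by the lack of site data. That reading is probably intended, so the point there is a clarification only.

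**Conclusion.** The point holds as a flaw in a stated rule. A request prompted by a signal would inform the EG, contrary to the intent of the confidentiality sentence. On planning values such a signal has a probability of about 8–12% at the first look and 28–35% at the second. These figures assume 24 months of follow-up, 1350 evaluable per arm, a rate ratio of 0.5, a normal approximation, and a request made when the guidance boundary is crossed. The finding itself rests on the wording and does not depend on them.

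Four stronger readings are tempting, and the documents do not support them.

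- **The first efficacy look coincides with the extension decision.** With follow-up to the end of the trial the look falls near month 20, after the 18-month accrual. The low rates that would prompt an extension delay it further.
- **The one-sided 0.025 level is no longer assured.** No inflation from an extension has been shown. The two interim looks with a final test at 0.025 give an overall one-sided level of 0.0253–0.0256, which is a separate matter and negligible.
- **Safety unblinding would be delayed.** No section describes a delay or a veto.
- **The DMC must be taken out of EG decisions.** Section {5d} says that without consensus "the matter will be discussed with the DMC and Scientific Advisory Board (SAB) in order to make a decision if necessary". It then introduces the DSMB as an additional body, and the abbreviation list gives the two separately, although the heading of {21a} treats the DSMB as the data monitoring committee. Whether they are one body is unresolved, and nothing says interim data enter those discussions.

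**What to change.** In {21a}, replace the unblinding clause with wording to this effect: the DSMB may obtain treatment allocation at any time on its own authority, through its independent statistician, without consulting or informing the Executive Group, which receives only the DSMB's recommendations.

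In {21b}, as a minor clarification, state that the event-rate review for extending recruitment uses the pooled rate only, to be compared with a planning value of about 16.9/1000/year at rate ratio 0.5.

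The cost is a wording change in the protocol and, where needed, the DSMB charter. The independent statistician is already a member. Access to the allocation, which {16b} limits to those with randomisation viewing rights, would have to be arranged in advance. Sample size, alpha and the interim boundary are unchanged.
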